#### Secondary outcome measures

1. Anxiety and worry about CVD risk is assessed by a 7-point Likert scale, ranging from 'not anxious/worried at all' to 'very worried/anxious'. These questions were used in an earlier study by Claassen et al. [13].

2. Illness perception is assessed by the Brief Illness Perception Questionnaire (Brief-IPQ) [47]. The Brief-IPQ consist of 8 items on the seriousness and impact of diabetes on various aspects of life, measured on a 10-point Likert scale ranging from 'strongly disagree' to 'strongly agree'. There is also 1 open question that asks patients to list what they consider the three most important causes for their disease.

3. Attitude and intention to change behaviour according to the Theory of Planned Behaviour [38] are measured by the Determinants of Lifestyle Behaviour Questionnaire, which was developed for a randomised controlled trial to investigate the effects of a cognitive behaviour programme on the primary prevention of T2DM and CVD [48]. The questionnaire consists of three parts, namely on the attitude and intention to change 1) dietary intake, 2) physical activity and 3) smoking behaviour. Each part has seven attitude items and three items on intention to change the specific behaviour. The attitude items have a 7-point scale. Examples of attitude items are: 'I consider eating healthier/increasing physical activity/quitting smoking good-bad, difficult-easy, frustrating-satisfactory'. The intention to change behaviour items have a 5-point Likert scale ranging from 'strongly agree' to 'strongly disagree'. An example is 'I intend to eat healthier/increase physical activity/stop smoking within two months'.

4. The Short Form Spielberger State Anxiety Inventory (SF-STAI) [49] consists of six items to assess the extent to which patients feel 'calm', 'tense', 'upset', 'relaxed', 'content', and 'worried' on a 4-point scale ranging from 'not at all' to 'very much'. Sum scores will range between 20 and 80 with higher scores indicating higher levels of anxiety.

5. Satisfaction with the communication is assessed by questions from the COMRADE scale [46]. This scale consists of 10 questions on a 5-point scale ranging from 'strongly disagree' to 'strongly agree'. These questions are only included in the second questionnaire, which is given at 2 weeks just after the visit to the diabetes nurse and dietician.

### Additional measurements

Physical examinations will be performed and blood samples are taken at baseline by medical assistants of the DCS at baseline in order to estimate the risk to develop cardiovascular disease by means of the UKPDS risk engine [44]. Systolic blood pressure is measured after 5 minutes of rest in seated position by Collon Press mate (BP-8800, Komaki-City). HbA1c will be measured by High Performance Liquid Chromatography and total cholesterol and HDL-cholesterol by means of enzymatic techniques (Boehringer-Mannheim, Mannheim, Germany). Age, duration of diabetes, sex, ethnicity, level of education, marital or cohabiting status, employment status, family history of T2DM and CVD and smoking status are included in the self-reported questionnaires. Smoking status will be distinguished in non-smoker, ex-smoker or current smoker including number of cigarettes per day.

### Sample size

The primary outcome measure is risk perception. Because we do not have the availability of a validated questionnaire it is not possible to use data of previous studies for the purpose of the power calculation. Therefore, we choose to use Cohen's effect sizes [50]. The power calculation is based on a difference of 0.5 standard deviations between the intervention and control group. The calculation is based on the Student's t-test for two independent groups.

The result is that we need 84 patients in each group to detect a difference of half a standard deviation with a power of 90%. Taking into account a possible dropout rate of 30% the number of patients in each group must be 120. In 2008, approximately 40 newly diagnosed patients per month were registered at the DCS, which means 480 patients per year. It is expected that not all patients are eligible and willing to participate in the study and therefore we preserve an inclusion period of 12 months.

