#### Primary outcome measure

Appropriateness of risk perception is the primary outcome measure. Risk perception will be measured by using a question from a questionnaire previously developed for the IMPALA study [46]. This question is 'If the mean risk of developing CVD in the next 10 years for men with diabetes is 20 of 100 men and for women 15 of 100 women, how would you rate your risk of developing CVD in the next 10 years?' In addition, at 2 and 12 weeks only, a population diagram will also be shown in the questionnaire. Patients will be asked to indicate how many of 100 people will develop CVD in the next 10 years.

Appropriateness of risk perception will be assessed by a comparison of the UKPDS score [44] of the patient with the risk perception. Appropriateness is considered as a patient with a high-risk perception while indeed having a high risk, or a patient with a low-risk perception while having a low risk [46]. According to the UKPDS risk engine, a risk of > 30% is considered high risk, a risk between 15 and 30% is an intermediate risk, a risk < 15% is a low risk.

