### Analyses

Comparability between the two groups will be assessed at baseline. On the basis of an intention-to-treat analysis, differences in changes between the intervention and the control group are measured with 95% confidence intervals at 2 and 12 weeks for both primary and secondary outcomes. For dichotomous outcome variables multilevel logistic regression analyses will be used. To calculate differences between continuous variables linear regression analyses will be used. If there are any relevant differences between the groups, we will adjust data for these factors (i.e. age, gender, diabetes duration, level of education and family history regarding T2DM and CVD).

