## Discussion

This article contains an extensive description of the design of the @RISK Study: an intervention to investigate the effects of a newly designed risk communication protocol on risk perception, attitude and intention to change lifestyle behaviour. We expect that due to the risk communication intervention, patients' appropriateness of risk perception will improve in a way that they will understand the meaning of their absolute 10 year risk to develop CVD, and subsequently develop a more positive attitude and intention towards lifestyle behaviour change. Risk communication is very relevant and important for patients with diabetes because nowadays patients are expected to make their own choices and decisions concerning their diabetes care.

Only a few studies on the effectiveness of risk communication on changing patients' risk perception and attitude on lifestyle changes have been performed. Brenner et al. performed a randomised controlled trial on risk communication in patients with hypertension and a CVD risk > 10%. The intervention included educating patients of their 10-year risk of myocardial infarction or death, illustrated by a graphical representation of the risk, and three follow-up phone calls by a physician or study nurse. This resulted in behaviour modification and in a significant reduction in CVD risk [51,52]. A randomised controlled trial by Koelewijn-van Loon et al. found that appropriateness of risk perception improved and anxiety reduced. They found no improvement in lifestyle in patients with high risk of developing CVD. As the risk communication was part of a large intervention study, it is unclear if the risk communication itself has caused the improvement [46,53].

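### The stated 90% power belongs to a t-test on a continuous risk perception score; it is not established for the defined primary outcome, a yes/no match

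*Protocol article*

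**What the plan says.** All references are to the protocol article.

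- **Primary outcome measure:** "Appropriateness of risk perception is the primary outcome measure". The patient's perceived risk is compared with the UKPDS score: "Appropriateness is considered as a patient with a high-risk perception while indeed having a high risk", or the same agreement at low risk. The abstract and the objectives name the same primary outcome.
- **Sample size:** "The primary outcome measure is risk perception". The effect is standardised: "The power calculation is based on a difference of 0.5 standard deviations between the intervention and control group". The test named is a two-sample Student's t-test. From these inputs the section concludes: "we need 84 patients in each group to detect a difference of half a standard deviation with a power of 90" per cent. This is raised to 120 per group for 30% dropout.
- **Analyses:** "For dichotomous outcome variables multilevel logistic regression analyses will be used"; continuous outcomes go to linear regression. The model for the primary outcome is not named. Results are to be given with 95% confidence intervals at 2 and 12 weeks.

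The article gives no proportion of patients with an appropriate perception, for either group, and does not state the alpha level or its sidedness.

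**The concern.** The sample size section and the outcome section describe two different variables. Perceived risk is a score with a mean and a standard deviation. Appropriateness, as defined, is a result that each patient either has or does not have. A standardised mean difference and a t-test describe the first and not the second.

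Nor does the first stand in for the second. The background section says that many patients underestimate their risk and that some are unrealistically pessimistic. To become appropriate, these two groups have to move in opposite directions. Mean perceived risk could stay the same while appropriateness improves, or shift while appropriateness does not.

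The 90% figure tells a reader how large an effect the trial was built to find, and so how to read a non-significant primary result. If it belongs to another variable, a null result on appropriateness could be taken as stronger evidence of no effect than it is.

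**Working it through.** **Inputs.** From the sample size section: 0.5 SD, 90% power, 84 evaluable per group, 30% dropout, 120 per group. Assumed: two-sided alpha 0.05, which the 95% confidence intervals suggest and which fits the stated size (one-sided 0.05 would need only 69 per group). Also assumed: the rates of appropriateness, shown as a range because the article gives none.

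**Step 1. The plan's own figure.** With n = 2(z₀.₉₇₅ + z₀.₉₀)² / d², n = 2(1.960 + 1.282)² / 0.25 = 84.06. Power at 84 per group is 89.98% by the normal approximation and 89.6% by the exact t-test (which needs 86 for a full 90%). Dropout: 84 / 0.70 = 120. The arithmetic is sound for a continuous score.

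**Step 2. A 0.5 SD shift in a normal score, cut into yes/no.** If the control rate is p₁, the intervention rate is p₂ = Φ(Φ⁻¹(p₁) + 0.5). With p̄ = (p₁ + p₂)/2, power for two proportions is

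Φ{ [ (p₂ − p₁)√n − 1.96√(2p̄(1 − p̄)) ] / √(p₁(1 − p₁) + p₂(1 − p₂)) }.

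Example, p₁ = 0.50, p₂ = 0.691, n = 84: [0.1915 × 9.165 − 1.96 × 0.694] / 0.681 = 0.58, and Φ(0.58) = 0.72.

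| Control rate | Intervention rate | Power, 84 per group | n per group for 90% |
|---|---|---|---|
| 10% | 21.7% | 55% | 202 |
| 20% | 36.6% | 67% | 153 |
| 30% | 49.0% | 72% | 137 |
| 40% | 59.7% | 73% | 133 |
| 50% | 69.1% | 72% | 136 |
| 60% | 77.4% | 69% | 147 |
| 70% | 84.7% | 63% | 168 |
| 80% | 91.0% | 53% | 213 |

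The range is 53% to 73%.

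**Step 3. Other ways to carry 0.5 over to a yes/no outcome, 84 per group.**

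- Odds ratio exp(0.5π/√3) = 2.48: 66% to 83% (control rates 20% to 70%).
- Half a standard deviation of the binary variable itself, 0.5√(p₁(1 − p₁)): 81% to 92% (control rates 20% to 50%).
- Cohen's h = 0.5: Φ(0.5√(84/2) − 1.96) = 90%. Here p₂ = sin²(arcsin√p₁ + 0.25), so control rates of 20%, 30%, 40%, 50% and 60% become 42.9%, 54.4%, 64.7%, 74.0% and 82.3%. The gains are 22.9, 24.4, 24.7, 24.0 and 22.3 points.

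**Step 4. What 84 per group can detect, by the formula in step 2.**

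| Control rate | Difference detectable at 90% power | Power for a 15-point difference |
|---|---|---|
| 20% | 23.0 points | 59% |
| 30% | 24.4 points | 52% |
| 40% | 24.7 points | 49% |
| 50% | 24.0 points | 50% |
| 60% | 22.4 points | 55% |

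Step 4 needs only an assumed control rate, not a conversion of 0.5 SD.

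**The case against.** The best defence is that the authors say they chose Cohen's effect sizes. For two proportions, a medium effect is h = 0.5, and on that reading 84 per group does give about 90%. This stands as far as it goes: a shortfall is not proven. But the section specifies standard deviations and a t-test, not h, and the gain of 22 to 25 points that h = 0.5 implies is neither stated nor justified.

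A reader might infer from step 2 that the true power is about 72%. The documents do not support that figure. It needs a normal score, a cut at or near the control median and a control rate near 50%, none of which is given. A single cut also does not model a match with the patient's own risk class when under- and over-estimators must move in opposite directions.

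A reader might also infer that usable earlier data existed, because the question comes from an earlier study and the discussion cites a trial that "found that appropriateness of risk perception improved and anxiety reduced". That is not shown. The stated reason is the lack of a validated questionnaire. The outcome section says the question was developed before, not that it was validated. The discussion gives no rate, and says that the part played by risk communication in that trial is unclear.

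Two smaller objections hold in part. The article never names the model for the primary outcome; logistic regression follows from the definition and the rule for dichotomous variables. Confidence intervals will be reported, which limits over-reading of a null result but does not make the power statement apply.

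This is not a detail left to an analysis plan: the article states a basis for its sample size, and that basis conflicts with the outcome it defines.

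**Conclusion.** The mismatch holds. The 90% power is correctly calculated for a continuous score compared by t-test, and is not established for appropriateness of risk perception. Without a stated control rate and target rate, power for the primary outcome is undetermined. At 84 evaluable per group it is about 53% to 73% if the 0.5 SD is a shift in a dichotomised normal score (control rates 10% to 80%), and about 90% if the effect is as large as h = 0.5, a gain of about 22 to 25 points (control rates 20% to 60%).

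These figures assume two-sided alpha 0.05 and a plain comparison of two proportions at one follow-up time, with no covariate adjustment and no allowance for the clustering that a multilevel model implies.

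**What to change.** In the sample size section:

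1. Name appropriateness of risk perception as the primary outcome, as the rest of the article does.
2. Replace the 0.5 SD and t-test statement with one for two proportions, for example: with 84 evaluable patients per group (120 randomised, 30% dropout) and two-sided alpha 0.05, the difference in the proportion with an appropriate risk perception that is detectable with 90% power is about 22 to 25 percentage points, for assumed control rates of 20% to 60%; power for a 15-point difference is about 50% to 59%.
3. State alpha and its sidedness, and say that the control rates are assumptions.

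The cost is wording only. No more patients are needed, but the stated power becomes less favourable.

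Making a continuous score primary, to suit the t-test, is not recommended. It would change the primary outcome of a registered trial that has been recruiting since March 2009, and the population-diagram answer is collected only at 2 and 12 weeks, so that item has no baseline.

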### Analyses

Comparability between the two groups will be assessed at baseline. On the basis of an intention-to-treat analysis, differences in changes between the intervention and the control group are measured with 95% confidence intervals at 2 and 12 weeks for both primary and secondary outcomes. For dichotomous outcome variables multilevel logistic regression analyses will be used. To calculate differences between continuous variables linear regression analyses will be used. If there are any relevant differences between the groups, we will adjust data for these factors (i.e. age, gender, diabetes duration, level of education and family history regarding T2DM and CVD).

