### Treatment allocation

For intervention allocation a randomization list is drawn up using a computerized randomization computer program (Random Allocation Software version 1.0.0). Patients are randomly assigned to either the intervention group, receiving the risk communication intervention in addition to the managed diabetes care or the control group, receiving managed diabetes care only. Approximately two weeks after the first visit, patients are scheduled for either the intervention or control session to the diabetes nurse and dietician. The manager of the DCS, who is not involved in the patients' care, allocates the patient to one of the two groups on the basis of the randomisation list. The flow of the patients will be registered by a medical assistant according to a flow diagram recommended by the CONSORT statement [43]. Participants may withdraw from the study at their own request and without providing reasons. Provided reasons for withdrawal will be registered. Figure 1 shows the design of the study.

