### Treatment fidelity

All diabetes nurses and dieticians were trained to perform the intervention and they all have contact with patients of both the intervention and control group. Due to practical reasons, (i.e the part-time availability of the diabetes nurses and dieticians) it was not possible to divide the caregivers into two groups.

To increase treatment fidelity we will take two measures. Firstly, we developed a protocol for both the intervention and control group that is obliged to use during the whole study period by all diabetes nurses and dieticians. Secondly, 20 tape-recordings (10 intervention patients and 10 control patients) are made to assess treatment fidelity of the diabetes nurses and dieticians.

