### Outcome assessment

Primary and secondary outcome measurements are assessed at baseline, and again after 2 weeks (directly after the intervention or control visit to the diabetes nurse and dietician) and 12 weeks by means of self-reported questionnaires.

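### Continuous outcomes get ordinary linear regression while dichotomous ones get a multilevel model, with no levels named and no reason given; one mixed model would be consistent and keep patients with one follow-up

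*Protocol article*

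**What the plan says.** All references are to the protocol article.

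- **Analyses.** Effects are defined so that "differences in changes between the intervention and the control group are measured with 95% confidence intervals at 2 and 12 weeks", on an intention-to-treat basis. Two models follow in adjacent sentences: "For dichotomous outcome variables multilevel logistic regression analyses will be used", and then "To calculate differences between continuous variables linear regression analyses will be used". The levels of the first model are not named, and the second sentence carries no multilevel qualifier.
- **Treatment allocation.** The patient is the unit of randomisation: "Patients are randomly assigned to either the intervention group, receiving the risk communication intervention in addition to the managed diabetes care or the control group".
- **Treatment fidelity.** All nurses and dieticians were trained in the intervention, and "they all have contact with patients of both the intervention and control group".
- **Outcome assessment.** "Primary and secondary outcome measurements are assessed at baseline, and again after 2 weeks"; a further questionnaire follows at 12 weeks.
- **Secondary outcome measures.** Most are scale scores: worry, illness perception, attitude, intention, state anxiety ("Sum scores will range between 20 and 80 with higher scores indicating higher levels of anxiety") and satisfaction. Satisfaction is asked only at 2 weeks.
- **Sample size.** 84 per group are needed for 0.5 SD at 90% power, raised to 120 per group for 30% dropout.

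**The concern.** Whatever structure led the authors to a multilevel model for dichotomous outcomes (visits within patients, patients within caregivers, or both) is present equally in the continuous outcomes. As worded, the two families of outcome in one report would rest on different error structures, and a reader cannot tell which level the authors thought mattered.

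Two things could be at stake:

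1. **Interval width.** The intervention is a conversation led by individual nurses and dieticians. If its effect depends on who delivers it, a model without that variation gives intervals that are too narrow for the effect across caregivers generally.
2. **Use of the data.** A regression of change fitted separately at each follow-up, without imputation, uses only patients who returned that questionnaire. A patient with a 2-week but no 12-week value contributes nothing to the 12-week estimate.

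The outcomes mainly concerned are the continuous secondary ones. Appropriateness of risk perception, if analysed as appropriate or not, already falls under the multilevel logistic model.

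**Working it through.** **Step 1. The plan's own figure.** Inputs from the Sample size section: difference 0.5 SD, power 90%, two-group t-test. Alpha is not stated there; two-sided 0.05 is assumed, in line with the 95% intervals.

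n per group = 2 × ((1.960 + 1.282) / 0.5)² = 84.06, against the stated 84. Then 84 / 0.70 = 120. Both figures reproduce, and neither depends on this point.

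**Step 2. Is a patient level needed for valid intervals?** The stated effect is a difference in change at 2 weeks and another at 12 weeks. Analysed one time point at a time, each patient supplies one change score, so within-patient correlation does not enter that interval. It would matter only if both follow-ups were pooled in one ordinary regression, which the text does not say.

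**Step 3. Is a caregiver level needed?** Caregivers are crossed with arm. With arms balanced within caregiver, an average-level effect cancels from the comparison: the true variance is 2(1 − ICC)σ²/n, while the ordinary model reports about 2σ²/n. At ICC 0.05 the reported standard error is then about 1/√0.95 = 1.026 times the true one, slightly conservative.

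A caregiver-by-arm effect does not cancel. If the intervention effect varies over J caregivers with variance τ², it adds about τ²(1/J + (1 − 1/J)/n) to the variance of the estimate.

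**Step 4. Simulation.** 84 per arm, individual randomisation, control-arm variance 1, no caregiver term in the analysis, 20,000 runs per row (Monte Carlo error about 0.15 percentage points, from √(0.95 × 0.05 / 20,000)). Numbers of caregivers and variances are assumptions.

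| Caregivers | Variance of average level | Variance of intervention effect | SD of estimate | Mean reported SE | Coverage |
|---|---|---|---|---|---|
| 6 | 0 | 0 | 0.1558 | 0.1541 | 94.9% |
| 6 | 0.05 | 0 | 0.1546 | 0.1534 | 95.1% |
| 6 | 0.10 | 0 | 0.1512 | 0.1528 | 95.2% |
| 10 | 0.05 | 0 | 0.1530 | 0.1536 | 95.1% |
| 10 | 0.10 | 0 | 0.1532 | 0.1532 | 94.9% |
| 12, balanced | 0.05 | 0 | 0.1508 | 0.1538 | 95.5% |
| 12, balanced | 0.10 | 0 | 0.1471 | 0.1534 | 96.0% |
| 6 | 0.05 | 0.02 | 0.1657 | 0.1540 | 93.3% |
| 10 | 0.05 | 0.02 | 0.1607 | 0.1545 | 94.0% |
| 6 | 0.05 | 0.05 | 0.1823 | 0.1550 | 90.5% |
| 10 | 0.05 | 0.05 | 0.1706 | 0.1555 | 92.6% |

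Hand check of the worst row (J = 6, τ² = 0.05):

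- Residual part: 0.95 × 2/84 = 0.0226.
- Average-level part: 0.05 × 2 × (5/6)/84 = 0.0010.
- Effect variation: 0.05 × (1/6 + (5/6)/84) = 0.0088.
- Sum 0.0324, square root 0.180, close to the simulated 0.182.

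**Step 5. Dropout.** 30% of 120 is 36 patients per group. If this is read as loss by 12 weeks, between 0 and 36 per group will have a 2-week value and no 12-week value; the documents do not say how many. Separate regressions leave these patients out of the 12-week comparison. A joint model of both follow-ups uses them.

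**The case against.** The strongest reply is that this is a matter of wording in a condensed article. Random-effects structure and missing-data handling are commonly left to the full protocol or analysis plan. The text never calls the linear model single-level, and the unnamed level may be visits within patients only, in which case the plan concedes nothing about caregivers. Individual randomisation and shared caregivers protect the comparison. The protocol also works against variation in delivery, with two half-day trainings, coaching on the job, a fixed protocol for each arm and tape-recordings. For the average effect among the caregivers of this one care system, the ordinary interval is acceptable; generalising to other caregivers is a different target. Finally, a caregiver-by-arm variance estimated from a handful of nurses is unstable and often comes out at zero.

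Most of this stands, and it rules out a stronger reading. A reader might infer that the intervals for most secondary outcomes are wrong. The documents do not support that: nothing in them gives a caregiver-by-arm variance or the number of caregivers, and without such variance coverage is about nominal. A reader might also apply the design effect 1 + (m − 1)ρ. With 6 nurses, m = 84/6 = 14; ρ = 0.02 gives 1.26 and a type I error of 8.1%, and ρ = 0.05 gives 1.65 and 12.7%. That formula treats every nurse-by-arm cell as an independent cluster, so the effect's own variance is 2ρ. If 2% or 5% means the variance of the effect, the simulated error is 6.7% or 9.5%.

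What the reply does not remove is the mismatch. The article states both models, side by side, for data of the same structure. That is something stated inconsistently, not a detail left out.

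**Conclusion.** The point holds as an unexplained inconsistency with a better method readily available. It is not a demonstrated error in the intervals.

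- If caregivers differ only in average level (ICC 0.05 to 0.10 assumed), coverage without a caregiver term is 94.9% to 96.0%.
- Coverage falls to about 90% to 94% only if the intervention effect varies by caregiver. This rests on assumed variances of 2% to 5% and 6 or 10 caregivers. Such variation is plausible for a nurse-delivered conversation, but the documents do not quantify it.
- The more dependable gain is in use of the data. With 30% dropout allowed for, a joint model keeps patients with one follow-up questionnaire and lets missingness at 12 weeks depend on the 2-week value. The size of that gain cannot be computed, because the split of dropout between the two follow-ups is not given. The model adds no outcome information for patients who miss both.

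**What to change.** 1. For continuous outcomes measured at both follow-ups, replace the linear regression of changes with a linear mixed model of the 2- and 12-week values. Include arm, time, arm-by-time and the baseline value as covariate, with a patient level. Report the arm difference with its 95% interval at each time point.
2. State the levels of the multilevel logistic model. Use the same structure for continuous outcomes, or give the reason for the difference.
3. Analyse satisfaction, measured only at 2 weeks, without a patient level.
4. Record which nurse and dietician saw each patient, and examine caregiver-by-arm variation as a sensitivity analysis only. With few caregivers that variance is too poorly estimated to drive the main analysis.

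Cost: a few sentences of analysis text, slightly more analysis work, and one or two extra data fields. The mixed model relies on data being missing at random given the baseline and observed follow-up values, which should be stated. Outcome collection and sample size do not change.

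### Covariates enter only after an undefined judgement of baseline imbalance, and the outcome's own baseline value is not on the list: this leaves the model to discretion and costs precision for continuous outcomes

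*Protocol article*

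**What the plan says.** All of this stands in the Analyses section of the protocol article unless another section is named.

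- The comparison, for primary and secondary outcomes alike: "differences in changes between the intervention and the control group are measured with 95% confidence intervals at 2 and 12 weeks".
- The trigger for adjustment: "Comparability between the two groups will be assessed at baseline".
- The rule: "If there are any relevant differences between the groups, we will adjust data for these factors". Nothing says what makes a difference relevant.
- The factors: "i.e. age, gender, diabetes duration, level of education and family history regarding T2DM and CVD". The abbreviation that opens the bracket makes this a closed list. The baseline value of the outcome is not on it.
- The models: "To calculate differences between continuous variables linear regression analyses will be used" and "For dichotomous outcome variables multilevel logistic regression analyses will be used". Neither sentence mentions a baseline term.
- The section Outcome assessment shows that the baseline values exist: "Primary and secondary outcome measurements are assessed at baseline, and again after 2 weeks".

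**The concern.** In a properly randomised trial, any difference between the arms at baseline is a chance event. A rule that changes the model when such a difference is seen lets chance choose the covariates. With no threshold for relevance, it also lets the analyst choose them after the data are in hand. The reader of the results could not tell from the plan which model should have been fitted.

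The rule also selects on the wrong property. A covariate is worth having because it predicts the outcome, not because it happens to differ between arms. The best predictor of a follow-up score is usually the same score at baseline, and the plan uses it only by subtraction. Subtraction fixes the slope on baseline at 1. When the true slope is lower, this adds noise, and a chance baseline difference carries over into the estimated effect.

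At stake are an analysis model that is not fixed in advance and, for the continuous outcomes, avoidable loss of precision.

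**Working it through.** **Inputs.** From the Sample size section: a difference of 0.5 SD, a two-sample t-test, 90% power, 84 per arm, and 120 per arm after 30% dropout. Assumed: two-sided alpha 0.05, in line with the 95% confidence intervals; equal SDs at baseline and follow-up; and a correlation r between baseline and follow-up, which the article does not give and is therefore shown as a range.

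**The plan's own figure.** n per arm = 2 × ((1.96 + 1.2816)/0.5)² = 84.06, and 84/(1 − 0.30) = 120. Both figures reproduce to within rounding.

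**How often the rule would fire by chance.** Counting the two family histories separately gives six factors. If they are independent, the chance that at least one differs under correct randomisation is:

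- at p<0.05: 1 − 0.95⁶ = 0.265
- at p<0.10: 1 − 0.90⁶ = 0.469

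The article names no test or threshold, so these two are illustrations.

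**Precision, continuous outcomes.** In units of the follow-up variance, the residual variance is:

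- follow-up score alone: 1
- unadjusted change score: 2(1 − r)
- follow-up adjusted for baseline (ANCOVA): 1 − r²

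Change relative to ANCOVA is 2(1 − r)/(1 − r²) = 2/(1 + r). This exceeds 1 for every r below 1. When r is below 0.5, 2(1 − r) is above 1, so the change score is then less precise than ignoring baseline altogether.

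**Power.** Reading 0.5 SD as the SD of the follow-up score, power = Φ(0.5/√(2v/84) − 1.96), where v is the residual variance. For r=0.3, the change score has v = 1.4, giving Φ(2.739 − 1.96) = 0.782; ANCOVA has v = 0.91, giving Φ(3.397 − 1.96) = 0.925.

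| r (assumed) | Variance ratio 2/(1+r) | Power, change | Power, ANCOVA |
|---|---|---|---|
| 0.2 | 1.67 | 72.6% | 91.1% |
| 0.3 | 1.54 | 78.2% | 92.5% |
| 0.4 | 1.43 | 84.1% | 94.2% |
| 0.5 | 1.33 | 90.0% | 96.3% |
| 0.6 | 1.25 | 95.2% | 98.2% |
| 0.7 | 1.18 | 98.7% | 99.5% |

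The follow-up score alone has 90.0% throughout. The t distribution changes little: 77.7% against 92.2% at r=0.3, and 89.6% against 96.1% at r=0.5.

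If instead 0.5 SD is the SD of the change, then v = 1 for the change analysis by definition, and its power is about 90% whatever r is. The variance ratio still holds.

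**Effect of the conditional rule.** A simulation used 84 per arm and six covariates related to the baseline outcome, and added to the change-score model only those that differed at p<0.05. Type I error across all methods and r = 0.3, 0.5 and 0.7 was 4.3% to 5.4%. At r=0.3, power was 78.4% for change, 78.2% for change with the conditionally chosen covariates, and 92.4% for ANCOVA. The rule therefore did not recover the lost precision.

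**The case against.** The strongest reply is that this is a condensed article. It names what is compared and the type of regression, not every model term. A regression of follow-up on arm and baseline also gives a baseline-adjusted difference in change, so a raw change-score analysis is an inference. That is fair, and the power loss is therefore conditional on an unadjusted change score. It does not rescue the covariate rule, which is stated outright: a fuller document that fixed the covariates in advance would contradict the article.

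A change-score comparison is also unbiased over repeated randomisation. This stands too; the argument against it is one of efficiency.

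Three stronger readings are tempting, and the documents do not support them.

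- A reader might infer that the conditional rule invalidates the confidence intervals or the type I error. Under a mechanical rule, the simulation shows no noticeable inflation. The candidates are also a closed set of pre-intervention factors. What remains is the discretion in an undefined term.
- A reader might infer that logistic regression cannot express a difference in change for a yes/no outcome. The article plans a multilevel logistic model, and outcomes are measured at three times. If visits are nested in patients, an arm-by-time term estimates a between-arm difference in change on the log-odds scale. The article does not state that term or the levels, but the model is possible.
- A reader might infer that the trial has only 78% power for its primary outcome. Appropriateness of risk perception, as defined under Primary outcome measure, is a match or no match between perceived and estimated risk. The variance formulas are for continuous scores, and no loss has been shown for this outcome.

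**Conclusion.** The concern holds in limited form. The article states an adjustment rule that depends on the observed data, has no criterion, and omits the baseline value of the outcome from its list. The consequences are an analysis model open to judgement after the data are seen and, for continuous outcomes analysed as unadjusted changes, a variance 2/(1+r) times that of a baseline-adjusted analysis.

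The size depends on r, which is not given. The loss is material at r of 0.4 or less, moderate around 0.5, and small at 0.7 or more. Any shortfall against the planned 90% arises only if r is below 0.5 and the 0.5 SD refers to the follow-up score; the article does not say which SD it means. The flagging rates of 26% and 47% assume six independent factors and the two illustrative thresholds. This should be corrected, but it does not invalidate the design.

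**What to change.** Replace the conditional sentence and the change comparison in Analyses with a model fixed in advance.

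1. For each outcome measured at baseline, model the follow-up value at 2 and 12 weeks on arm, with the baseline value of that outcome as a covariate. Use linear regression for continuous outcomes. For dichotomous outcomes, including the primary, keep the planned multilevel logistic model and add baseline status as a covariate.
2. Always include the listed factors (age, sex, duration of diabetes, education, and family history of diabetes and of cardiovascular disease) as a fixed set. A choice of always or never would leave the decision open. It matters most for the logistic models, where adjusted and unadjusted odds ratios estimate different quantities.
3. Delete the imbalance trigger. Baseline comparability can still be described in a table, without bearing on the model.
4. Compare outcomes without a baseline value at follow-up with the same fixed covariates. These are satisfaction with the communication, asked only in the second questionnaire, and the population-diagram item, shown only at 2 and 12 weeks.

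The cost is wording. The baseline outcomes and the listed factors are already collected (Outcome assessment; Additional measurements), so no visit, measurement or patient is added.
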